**Flowchart of study.**

### Intervention design

After randomisation, researchers will conduct focus group discussions with parents, Stage 3 (year 5 and 6) students, and individual interviews with teachers. This qualitative research will aim to investigate the results of the baseline data collection and inform the intervention design with these schools. These focus groups and interviews will unpack the positive and negative aspects of the school’s utilisation of sun-safe hats, sunscreen and staff role modelling of sun-safe behaviours.

Interviews and focus groups will also investigate schools’ understanding of being ‘SunSmart’ and other aspects of the existing school sun protection policy; including sun-safe school uniforms, the provision of shade, scheduling of outdoor activities, sun protection within the school curriculum and finally, inclusion of the local community into school sun-safe practices. This broader context will allow analysis of the relative importance of the three specific study outcomes and other factors that may have influenced the baseline results.

Data from this formative research will be analysed using coding and intra and inter-textual analysis to ascertain common themes across schools [16]. Formative interview data will be utilised to refine the design and enactment of the intervention.

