The intervention development and implementation will be based on Social Cognitive Theory (SCT) [17] which focuses on the interplay between personal, behavioural, and environmental factors. The personal factors identified in SCT (such as the thoughts, emotions and biological dispositions of an individual) will be addressed by the intervention program by influencing the value systems that may reinforce the low emphasis on the school sun protection policy. The nuanced behavioural factors associated with sun protection behaviours, such as the wearing of hats and sunscreen and playing in shaded areas also need to be identified objectively and addressed within the intervention program. Finally, the environmental factors (both social and physical) that often exist beyond the immediate control of individual schools need to be identified and addressed in order to remove potential barriers and to provide opportunities for social support. An example of influencing this factor may include the utilising and modifying of existing school infrastructures that were not used by the school in order to make them more accommodating for the sun-safe practices without any additional financial outlay.

The intervention will also be based on the key principles of the WHO Health Promoting Schools (HPS) Framework [18] that focuses on the connection between formal curriculum, school ethos and the school-home-community partnership. By addressing these overlapping and interconnecting components, schools are more likely to provide comprehensive and effective health promotion throughout the entire school community. The formal curriculum of the HPS framework refers to the teaching and learning programs provided by the school, and advocates these be distributed in a variety of subjects and classes rather than just traditional health education classes [19]. A school ethos is derived by the components put in place which construct its values and atmosphere, including organisation, environment, policies and procedures [19]. The partnership between the school and local community is a vital component for school health promotion. By incorporating families and the community into the life of the school, a supportive learning and healthy environment can be established [19].

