Direct observations will be made in designated Target Areas that represent all standard locations likely to provide opportunities for students to have sun exposure during their recess and lunch periods (e.g. play equipment or outdoor sporting fields/courts). These Target Areas (one shaded and one non-shaded) will be predetermined and identified for observations prior to baseline assessments. A map will be provided to identify Target Areas and a standard observation order established for each school. Additional Target Areas may be added by observers on site and then documented.

During occasions of high student density, Target Areas will be subdivided into smaller Scan Spaces so that accurate measures can be obtained. Observers will use standard court or field markings to determine appropriate Scan Spaces within each Target Area. Data from these smaller spaces will be summed to provide an overall measure for each Target Area. A decision to subdivide a Target Area depends upon the (1) number of students in the area and (2) the type of student activity.

Additional data recorded prior to the direct observation scans includes;

1. Temperature and UV level at the start and end of the observation period; 2. Whether the observation was made at recess or lunch; 3. Start and finish times of recess and lunch; and 4. The condition of the target area. This is coded as follows:

A = Area is accessible (e.g. not locked or rented to others).

U = Area is usable for activity (e.g. is not excessively wet or windy).

SS = Area is supervised by designated school personnel who are role modelling sun safe behaviour (e.g. wearing a broad brimmed hat, wearing a shirt with a collar and minimum short sleeves, sunglasses, using shade).

SN = Area is supervised by designated school personnel who are not role modelling sun safe behaviour.

O = Organised physical activity (i.e. scheduled, with leadership by school personnel apparent) is occurring in the area (e.g. intramurals, interscholastic practices, fitness stations).

E = Equipment provided by the school or other agency is present (e.g. balls, jump ropes). This will not be coded as present if the only equipment is permanent (e.g. basketball hoops).

C = Covered area (e.g. the activity is taking place in an area where at least 50% of the target area is covered with shade provided by a permanent or natural feature such as shade cloth or tree foliage).

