### Statistical methods

Statistical analysis of the primary and secondary outcomes will be conducted with linear mixed models using SPSS statistics version 20 (IBM SPSS Statistics, 2012) and alpha levels will be set at *p* > 0.05.

The models will be used to assess the impact of treatment (SunSmart Policy Intervention or Control), time (baseline, post-test and follow-up) and the group-by-time interaction, these three terms forming the base model. The models will be specified to adjust for the clustered nature of the data and will include all randomised participants in the analysis. Mixed models are robust to the biases of missing data and provide appropriate balance of Type 1 and Type 2 errors [22]. Mixed model analyses are consistent with the intention-to-treat principle, assuming the data are missing at random [23]. Sex, temperature/UV, time of day, type of period (recess or lunch) and conditions of target area (as previously outlined) will be included as covariates in the models.

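### The outcome models adjust for supervisors' role modelling measured after randomisation, so the treatment term is net of role modelling and not the total policy effect

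*Protocol article*

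**What the plan says.** Statistical methods (protocol article) specifies linear mixed models for the primary and secondary outcomes. Treatment, time and their interaction form the base model. Among the covariates, it states that "conditions of target area (as previously outlined) will be included as covariates in the models".

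The earlier outline is in Wearing of headwear and prevailing environmental conditions: "The condition of the target area. This is coded as follows". The codes are A (accessible), U (usable), SS, SN, O (organised activity), E (equipment) and C (covered). Two of them describe the supervising adult: "SS = Area is supervised by designated school personnel who are role modelling sun safe behaviour" and "SN = Area is supervised by designated school personnel who are not role modelling sun safe behaviour". Code C applies where "at least 50% of the target area is covered with shade".

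Intervention design says the formative work will examine each school's "utilisation of sun-safe hats, sunscreen and staff role modelling of sun-safe behaviours", and then speaks of the "relative importance of the three specific study outcomes". The Background lists encouragement of role modelling by teachers as part of the SunSmart Program. The Discussion gives the primary aim as evaluating the impact of the policy intervention on children's sun protection behaviour at school. It also lists teacher role modelling among the covariates.

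**The concern.** A covariate that the intervention may change does a different job from sex or weather. If a better policy leads teachers to wear hats in the playground, and children follow, that is part of the policy's benefit. A model that holds the teacher's behaviour fixed takes that part out of the treatment term and assigns it to the covariate.

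Two things are at stake. First, the main result would answer a narrower question than the stated aim. Second, adjustment for a variable measured after randomisation gives up some of the protection of randomisation. Anything that drives both role modelling and hat wearing at follow-up, such as a principal's commitment, can bias the adjusted term in either direction.

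The same variable is also placed in two roles, as a study outcome in one section and as an adjustment variable in another.

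**Working it through.** No figure in the document is at issue, so there is none to reproduce. The check is a trace through the text, followed by an illustration with assumed values.

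**1. Is SS/SN in the model?** Statistical methods refers back to an earlier outline of target-area conditions. The article has only one, and SS and SN are on it. The Discussion's mention of role modelling as a covariate confirms the reading.

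**2. Is it measured after randomisation?** The codes are recorded before the scans at each observation. Outcomes places assessments at baseline, 12 months and 15 months. Recruitment and study participants places randomisation after baseline. The 12- and 15-month codes are therefore post-randomisation, and nothing restricts the covariate to baseline values.

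**3. Can the intervention affect it?** Role modelling is a programme component (Background), a topic of the formative work that shapes the intervention, and one of the three outcomes referred to there (Intervention design).

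**4. What does the treatment term then estimate?** Let a be the change in the prevalence of role modelling caused by the intervention, b the effect of role modelling on the proportion wearing hats, and c the effect by all other routes. Under a linear model with no common causes of role modelling and hat wearing:

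- total effect = c + a × b
- group-by-time term with SS/SN in the model = c
- share removed = a × b / (c + a × b)

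**5. Illustration.** The document gives none of a, b or c, so all values below are assumed.

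| a | b | c | Total | Net of SS/SN | Share removed |
|---|---|---|---|---|---|
| 0 | 0.20 | 0.10 | 0.10 | 0.10 | 0% |
| 0.30 | 0 | 0.10 | 0.10 | 0.10 | 0% |
| 0.10 | 0.20 | 0.10 | 0.12 | 0.10 | 0.02/0.12 = 17% |
| 0.30 | 0.20 | 0.10 | 0.16 | 0.10 | 0.06/0.16 = 38% |
| 0.50 | 0.20 | 0.10 | 0.20 | 0.10 | 0.10/0.20 = 50% |
| 0.50 | 0.20 | 0 | 0.10 | 0 | 100% |

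A simulation with the trial's layout (5 intervention and 15 control schools, 24 observations per school at each of two time points, school fixed effects) agrees. For a = 0.30, b = 0.20 and c = 0.10 the mean group-by-time estimate was 0.159 without the role-modelling covariate and 0.098 with it. In the row with a = 0 the two estimates were 0.101 and 0.102, and in the row with b = 0 both were 0.101.

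**6. Do the other codes share the problem?** Shade is named as a policy element in the Background and in Intervention design, and "utilising and modifying of existing school infrastructures" is given as an example of what the intervention may include. Against that, each school's Target Areas are chosen before baseline as one shaded and one non-shaded, which fixes much of code C by design. No section names organised activity, equipment, accessibility or usability as something the intervention is to change.

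**The case against.** **The base model already gives the total effect.** It contains only treatment, time and their interaction, and the article never uses the term primary model. That is a fair reading of the label. However, the same paragraph says the covariates will be included, and nothing makes the unadjusted fit the one that carries the conclusion. An analyst following the text would report the adjusted term.

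**The covariate list is a loose summary.** It nominally covers the sunscreen outcome too, which is weighed by container over 50 days and has no target area or break period. This shows that the wording is condensed. It does not remove SS/SN from the hat-wearing model, where the codes do apply.

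**Role modelling is not formally designated as an outcome.** Hats are named as primary and sunscreen as secondary, and the intervention's content is settled only after the formative work. This stands as a limit on how large the effect on role modelling will be. It does not answer the point, because Intervention design still counts role modelling among the three outcomes.

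**Other covariates could be moved as well.** Scheduling of outdoor activities is part of the SunSmart Program, so UV or time of day at observation could in principle shift. The article does not say that breaks will be moved, and neither variable is called an outcome. The case against them is far weaker.

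**Stronger readings that the document does not support.** A reader might infer that every target-area condition is an intervention target and should be dropped. The text does not support this for A, U, O or E, and supports it only in part for shade. A reader might also infer a definite bias toward no effect, or express the loss as a share of a 20-point target by multiplying d = 0.4 by the SD of 0.5. The direction depends on a positive path through role modelling, the article gives no unit for that SD, and no inputs for the size of the path are given.

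**Conclusion.** The point holds for SS/SN. As written, the plan conditions the treatment effect on hat wearing on supervisors' role modelling measured after randomisation, and so estimates an effect net of role modelling and not the total policy effect that is the stated aim.

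Attenuation follows only if the intervention improves role modelling and role modelling raises hat wearing. The document gives no basis for its size. The assumed values above run from no loss to complete loss, and they are not a prediction for this trial. For shade the concern is weaker and extends only to the use of the current code C in place of the pre-baseline classification.

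This should be fixed, because it decides what the main result means. It does not invalidate the design, since the data needed for the right model are already to be collected.

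**What to change.** In Statistical methods, state that the primary estimate comes from a model with treatment, time, group-by-time, sex, temperature/UV, time of day, type of period and the pre-set area type (shaded or non-shaded, as classified before baseline), without post-randomisation SS/SN. Where shade is adjusted for, use that pre-baseline classification and not the current code C.

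Analyse SS/SN by arm as an outcome in its own right, in line with Intervention design. Report the model that adds SS/SN only as a labelled secondary or mechanism analysis, with a note that its treatment term is net of role modelling and open to confounding.

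The cost is a change of wording and possibly slightly less precision. No new data are needed.

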### Qualitative methods

The focus groups and interviews of Stage 3 students, parents and teachers will be used for the intervention design and will be digitally recorded with the participants’ consent and transcribed verbatim into a Microsoft Word document. Two computer programs (NVIVO 10 and Leximancer) will be used to assist with the organisational aspects of data analysis. Analysis will be conducted by members of the research team using a standard general inductive approach to qualitative analysis with NVIVO 10 and a specialised method of transforming lexical co-occurrence information from natural language into semantic patterns for qualitative analysis with Leximancer. The algorithms used by Leximancer are statistical, but they employ nonlinear dynamics and machine learning methods and have been validated, deemed stable, and reproducible [24].

## Discussion

The primary aim of this study is to evaluate the impact of a SunSmart policy intervention on children’s daily school sun protection behaviours. The study will use a novel evaluation strategy that directly observes the behaviour of children and teachers in their natural school environments. Researchers will also monitor sunscreen consumption over a ten-week time period in Grade 6 students during three summer intervals.

Previous school-based health promotion intervention studies have highlighted the importance of teacher and parental behaviour on health related intervention outcomes in primary school children [25]. A critical aspect of this study is that teachers, parents and the students themselves will be involved in the intervention design phase. Teacher, student and community ownership of intervention design has been identified in previous studies as a desirable factor to improve the effects of school-based interventions [26]. This ownership of the program has the potential to lead to greater sustainability of increased sun protection practices and enable teachers to integrate effective sun protection policies into the school day.

A clear strength of this study is the rigorous evaluation process including quantitative and qualitative measures to explore program feasibility and potential efficacy. The empirically robust design with baseline, post-test and follow-up measures will help examine the views of participants (teachers, parents and students), and help distinguish between an intervention that is poorly designed and one that may be poorly delivered [27]. We consider this a necessity in this study due to the multi-site delivery.

To our knowledge, no previous interventions have reported the effects of a policy-based intervention on sun protection behaviour outcomes using direct observation measures. Significantly, our study will be capable of collecting a host of covariates on the sun safety behaviour of primary school children namely daily temperature, period of UV exposure during recess and lunch periods, size of play area, nature of play children undertake and teacher role-modelling behaviour.

An additional study strength is the use of an objective measure of behaviour. Direct observation has a number of advantages over other possible measurement tools [28]. First, it is an objective method that provides contextually rich data to identify other factors related to sun protection behaviours (e.g., physical and social factors). Second, it can provide information on the type of hats being worn by children. The main disadvantage of direct observation is the time-intensive nature of observer training and data coding. The use of a direct observation instrument like iSOPARC is advantageous when working with children because unlike self-report measures of behaviour, they help eliminate language and literacy difficulties, recall bias and social desirability bias [29]. As research assistants will be blind to the randomisation of schools there is little to no chance of any bias impacting on the observations.

The findings of study will provide valuable information for other research groups looking for evidence based research on sun protection behaviours of primary school students in NSW. School-based sun behaviour interventions are infrequent, and seldom published in peer-reviewed journals. This study has the potential to change school policy and practice in relation to sun safety integration and enhance a range of key health promoting behaviours in schools.

## Abbreviations

NSW: New South Wales
UV: Ultraviolet
WHO: World Health Organization
NSWDEC: New South Wales Department of Education and Communities
CCNSW: Cancer Council NSW
SERAP: State Education Research Approvals Process
ACTRN: Australian and New Zealand Clinical Trials Registry Number
CONSORT: Consolidation Standards of Reporting Trials
SCT: Social Cognitive Theory
HPS: Health Promoting Schools
SOPARC: System for Observing Play and Recreation in Communities
TGA: Therapeutic Goods Administration
SPSS: Statistical Package for the Social Sciences
